**Legend:**
^*^Where unassisted breathing begins on Day 27 or Day 28, data will be recorded up to Day 29 or Day 30 respectively. ICU = intensive care unit.
^#^Further definition of safety outcomes:
^i^Defined as overt bleeding on upper GI endoscopy, developing as a complication in the ICU and accompanied by 1 or more of the following features within 24 hours: a. spontaneous drop of systolic, mean arterial pressure or diastolic blood pressure of 20 mmHg or more, b. start of vasopressor or a 20% increase in vasopressor dose, c. decrease in haemoglobin of at least 2 g/dl, d. transfusion of 2 units of packed RBC or more
^
30
^;
^ii^Bronchoconstriction requiring nebulised bronchodilators during or up to 30 minutes following nebulisation
^
31
^;
^iii^Ventilator or circuit dysfunction with respiratory deterioration - This may include hypoventilation, hypoxaemia, or other signs of respiratory deterioration temporally associated with ventilator or ventilator circuit dysfunction
^
32
^;
^iv^Hypoxaemia during nebulisation - A drop in SpO
_2_ to below 90% during or up to 30 minutes following nebulisation
^
31
^ requiring an increase in FiO
_2_

Further detail regarding presentation of outcome data is available in the Statistical Analysis Plan (SAP) (available at
https://nictu.hscni.net/service/march-trial/march-trial-documents/).

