Re-intubation	Event of reintubation of endotracheal tube after a planned extubation; Excludes temporary reinsertion of endotracheal tube for procedures only; Censored at 60 days
Respiratory physiotherapy input	Occurrence and frequency of airway clearance sessions; Censored at Day 28 (or the primary outcome is reached), or ICU discharge, or death, whichever comes first *
Antibiotic usage	Dose of individual agents Censored at Day 28 (or the primary outcome is reached), or ICU discharge, or death, whichever comes first *
Duration of ICU and hospital stay	Time from randomisation until patient first leaves the relevant facility or dies Censored at 6 months
All-cause mortality	Confirmation and cause of death
Safety ^ # ^	i) Clinically important upper gastrointestinal (GI) bleeding due to peptic ulceration confirmed on upper GI endoscopy ^ i ^ ii) Bronchoconstriction requiring nebulised bronchodilators ^ ii ^ iii) Ventilator or circuit dysfunction with respiratory deterioration ^ iii ^ iv) Hypoxaemia during nebulisation ^ iv ^ Censored at Day 28 (or the primary outcome is reached), or ICU discharge, or death, whichever comes first *
Hospital resource use	Number of days at Level of Care 0/1/2/3 Censored at 6 months
Time of consent to continue	
Health-related quality of life	EQ-5D-5L
60 days	
Health-related quality of life	EQ-5D-5L
All-cause mortality	Confirmation and cause of death
6 months	
Health-related quality of life	EQ-5D-5L
All-cause mortality	Confirmation and cause of death
Health service use since hospital discharge	Categories: care at hospital, emergency, GP surgery, health clinic, or other community setting, health care at home, medication

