### Assignment of interventions: Blinding

MARCH is a prospective, randomised, open label, unblinded trial. Patients, healthcare providers, and outcome assessors, will not be blinded to the allocated intervention in this trial in order to reflect routine practice when mucoactives are (or are not) used in critical care
^
36
^. The trial statistician, who has no role in decision-making with regards the conduct of the trial, will be unblinded and this will also facilitate linkage with the Data Monitoring and Ethics Committee (DMEC). The remainder of the trial team will also be unblinded for the purposes of managing data collection, reviewing cases to assess protocol deviations, and to undertake pharmacovigilance duties. As the trial design is open label, there is no unblinding procedure.

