### Adverse event reporting and harms

As the MARCH trial is recruiting a population that is already in a life-threatening situation, it is expected that many of the participants will experience adverse events (AEs) and serious adverse events (SAEs). Events that are expected in this population will not be reported as an AE e.g. death, agitation, delirium, organ failure and nosocomial infections. Events that are collected as safety outcomes for the MARCH trial also will not be reported as AEs. Only SAEs that are related to the mucoactive will be reported (i.e. serious adverse reactions (SARs)). A SAE will be defined as related to the mucoactive if it is assessed as being possibly, probably, or definitely related to the mucoactive, and reported within 24 hours of the investigator becoming aware of the event. The reporting period for the trial begins upon administration of the mucoactive and ends upon termination of the mucoactive. Termination of the mucoactive will usually occur at Day 28 (or when the primary outcome is reached), ICU discharge, or death, whichever comes first. Further details are provided in the Trial Protocol (
2024_12_02_MARCH Protocol_Final V4.0, available at
https://nictu.hscni.net/service/march-trial/march-trial-documents/).

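### The nebulisation hypoxaemia outcome requires a rise in FiO2, so a desaturation in a patient already at FiO2 1.0 cannot be counted

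*Protocol article*

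**What the plan says.** **Hypoxaemia.** Table 1 of the protocol article lists four safety outcomes, and its legend defines them. Outcome iv has two parts joined together. SpO2 must drop below 90% during nebulisation or within 30 minutes after it, and the drop must be one "requiring an increase in FiO" (the subscript 2 follows in the source). The article gives no alternative for a patient whose FiO2 is already at its maximum, and none for a response other than FiO2.

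**GI bleeding.** Table 1 names outcome i as "Clinically important upper gastrointestinal (GI) bleeding due to peptic ulceration confirmed on upper GI endoscopy". The legend adds: "Defined as overt bleeding on upper GI endoscopy, developing as a complication in the ICU and accompanied by 1 or more of the following features". The four features, a to d, concern blood pressure, vasopressor use, haemoglobin and transfusion.

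**Context.** Under Assignment of interventions: Blinding, "Patients, healthcare providers, and outcome assessors, will not be blinded to the allocated intervention". Under Adverse event reporting and harms, "Events that are collected as safety outcomes for the MARCH trial also will not be reported as AEs". The same section limits SAE reporting to events judged related to the mucoactive, within a reporting period that runs from its first administration to its termination.

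**The concern.** FiO2 has a ceiling. An outcome that needs FiO2 to go up cannot register an event in someone already at 1.0, and these are the patients with least room to tolerate a desaturation. The eligibility criteria do not exclude them. The population is ventilated acute respiratory failure, PaO2/FiO2 ratio is a planned subgroup variable, and the primary outcome counts time on extracorporeal lung support.

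Hypertonic saline is the nebulised study agent, so outcome iv bears directly on its safety. Secondary objective 1 includes safety outcomes, and the Discussion presents the trial as able to prevent harmful use. A definition that cannot see events at the FiO2 ceiling weakens what can be said on that question.

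For GI bleeding the issue is one of ascertainment. Whether a bleed enters the count depends on whether an endoscopy was done. The article states no rule for when it is done, and the clinicians know the allocation.

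**Working it through.** The article gives no expected rate or power for any safety outcome, so there is no stated figure to reproduce for this point. The check is a reading of the definitions, followed by an illustration on assumed values.

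**1. Can the event be met at FiO2 1.0?** Outcome iv = (SpO2 < 90% in the window) AND (FiO2 increased).
- Patient at FiO2 0.6, SpO2 falls to 85%, FiO2 raised: both true, counted.
- Patient at FiO2 0.6, SpO2 falls to 85%, nebuliser interrupted or other support raised, FiO2 unchanged: second false, not counted.
- Patient at FiO2 1.0, SpO2 falls to 75%: second cannot be true, not counted.

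The last result follows from the wording alone.

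**2. Does another part of the article count that patient?**
- Outcome iii includes hypoxaemia with no FiO2 condition, but only when linked in time to ventilator or circuit dysfunction.
- Outcome ii covers bronchoconstriction needing nebulised bronchodilators, a different event.
- A serious adverse reaction report needs the event to be serious and judged related by an unblinded investigator. It starts with mucoactive administration, so it gives no comparison with usual care alone.

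None supplies the missing between-group count.

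**3. Size, on assumed values.** Each factor level has 2 × 489 = 978 patients. Let p be the true proportion with an event and f the share of events that the FiO2 condition cannot register. Counted = 978 × p × (1 − f).

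| p (assumed) | True events | f = 5% | f = 10% | f = 20% |
|---|---|---|---|---|
| 5% | 48.9 | 46.5 | 44.0 | 39.1 |
| 10% | 97.8 | 92.9 | 88.0 | 78.2 |

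So about 2 to 10 of 49 events, or 5 to 20 of 98, would go unregistered. If f is the same at both levels of a factor, the risk ratio is unchanged, because p1(1 − f) / [p0(1 − f)] = p1/p0. The risk difference shrinks to (1 − f)(p1 − p0). Nothing in the article shows that f differs by group.

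**4. GI bleeding.** Let e be the share of bleeds that are scoped. With equal true bleeding, the observed risk ratio is e1/e0.
- e = 60% at both levels: 0.60/0.60 = 1.0, with 40% of bleeds missed.
- e = 70% against 50%: 0.70/0.50 = 1.4. At an assumed true rate of 2% this is 978 × 0.02 × 0.70 = 13.7 against 978 × 0.02 × 0.50 = 9.8 events.

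The 1.4 is simply the assumed scoping ratio. The article gives no scoping rates, so this shows a mechanism and is not evidence of bias.

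**5. Sample size.** Freedman's formula with hazard ratio 0.86, two-sided 0.05 and 90% power gives 1855, or 1856 as a multiple of four. Then 464/0.95 = 488.4, rounded up to 489, and 4 × 489 = 1956. The plan's figures reproduce, and this point does not touch them.

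**The case against.** The strongest reply is that events outside the definition are not lost. Reasons for missed doses are collected daily and the reason for stopping a mucoactive is recorded, so a desaturation that leads to withheld doses leaves a trace. A rating of merely possible relatedness is enough for a serious adverse reaction report. All-cause mortality and cause of death are collected. This stands as far as it goes: these data exist. They do not form a count of nebulisation desaturations that can be compared between groups, and pausing a single dose may leave no record.

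Second, endoscopic confirmation is a defensible choice in an open-label trial, because it trades sensitivity for an objective finding. A count without endoscopy rests on bedside recognition by the same unblinded staff, and a pressure drop or a vasopressor increase has many causes in intensive care. This stands, and it is why the bleeding definition should not be replaced.

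Third, the article is condensed and sends further detail on harms to the full protocol, which is not shown. Guidance for patients at maximum FiO2 could sit there. That is possible, but the definition printed in the article is stated without any such exception.

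A reader might also infer more than the article supports:
- *The sickest patients cannot have an endoscopy.* No section says so. The impossibility is strict only for FiO2 at its ceiling. For bleeding, all that follows is that a bleed without endoscopy is not counted, whatever the reason.
- *Cases just outside a definition are removed from adverse event reporting.* The exemption covers only events that are collected as safety outcomes, and a case that fails the definition is not one of those. The limit to related SAEs is a separate, general rule.

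**Conclusion.** The point holds for hypoxaemia. As worded, outcome iv cannot register a desaturation in a patient already at FiO2 1.0, and it also misses one answered only by interrupting the nebuliser or by another rise in support. The count is understated in patients with no FiO2 reserve. By how much is unknown: the 5% to 20% range is an assumption, and no between-group bias is shown.

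For GI bleeding only the narrower statement holds: the outcome counts scoped bleeds, and the decision to scope lies with clinicians who are not blinded. It would be wrong to conclude that the comparison is biased by any given amount, since the article gives no sign that endoscopy use differs by allocation.

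Both are ascertainment limits in secondary safety outcomes. The primary analysis and sample size are unaffected.

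**What to change.** **Hypoxaemia.** Amend the definition of outcome iv so that a fall in SpO2 below 90% in the stated window also counts when FiO2 is already 1.0, or when it leads to another increase in respiratory support or to interruption of the nebulisation. Report events meeting the current definition separately, so that both counts are visible. This changes what is recorded and not how patients are managed.

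**GI bleeding.** Keep the endoscopic definition. Where the records allow, report as supportive information, per group, the number of patients who had upper GI endoscopy and the number with overt bleeding meeting features a to d without it.

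**Cost.** One clause in a definition, a small addition to data capture and some extra tabulation. The hypoxaemia count becomes slightly broader, and the supportive bleeding count is less specific for peptic ulceration. Timing is the main limit: by 31 January 2025, 1820 of 1956 patients (93%) were enrolled, leaving 136. For those already enrolled the NHS record is the source document, but nothing in the article shows that brief desaturations around each nebulisation can be retrieved from it. Recovery may be partial, and the report should say so.

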### Participant timeline

The participant timeline is presented in
Table 2.

**Table 2. T2:** Participant timeline.

	STUDY PERIOD										
	Pre-Randomisation		Intervention Period						Consent to Continue	Follow-Up	
Timepoint	Pre- Baseline	Baseline/ Day 0	Day 1	Day 2	Day 3	Days 4–6	Day 7	Days 8–28 *		Day 60 (± 14 days)	6 Months (± 14 days)
ENROLMENT											
Eligibility assessment	X										
Informed consent	X										
Enrolment/ randomisation		X									
INTERVENTIONS											
IMP administration ^ # ^			X	X	X	X	X	X			
ASSESSMENTS											
Baseline data		X									
Daily data			X	X	X	X	X	X			
Blood and/or sputum sampling (optional)		X			X		X				
Adverse events			X	X	X	X	X	X			
Health-Related Quality of Life (EQ-5D-5L)									X	X	X
Health Service Use											X
Mortality			X	X	X	X	X	X		X	X

**Legend:** IMP = investigational medicinal product. #: IMP = carbocisteine, or hypertonic saline, or a combination of carbocisteine and hypertonic saline. *: Where unassisted breathing begins on Day 27 or Day 28, IMP will be administered up to Day 29 or Day 30 respectively.

### Sample size

The total sample size is 1956 (489 in each of the four randomised groups). The sample size has been calculated using a median duration of mechanical ventilation of 7 days
^
4,
21
^ with a minimal clinically important difference of 1 day
^
22
^, resulting in a median duration of 6 days in the three intervention groups. This minimum clinically important value is also based on discussion with patient and family member advisors, who emphasised the importance of reducing time spent on the ventilator as a priority outcome
^
23
^. This median duration of mechanical ventilation and 1 day reduction treatment effect result in a hazard ratio of 0.86. Based on a log-rank test and at 90% power and a significance level of 0.05, this requires a sample size of 1856 (464 in each of the four randomised groups). Previous critical care trials have demonstrated low levels of loss to follow-up, at less than 5%
^
24–
28
^, and the nature of the proposed trial where all primary outcome data will be acquired whilst patients are in the ICU and identifiable to the research team, should minimise loss to follow up. Allowing loss to follow at the 5% level, requires a sample size of 1956 (489 in each of the four randomised groups).

As there is no clinical or biological rationale for, or expectation of, any interaction between the two mucoactives, the sample size has not been inflated for this purpose. This is in keeping with systematic review findings highlighting appropriate restriction of the factorial design to scenarios where treatments do not have the potential for substantive interaction
^
29
^.

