**Methods:**

A UK multi-centre, 2x2 factorial, randomised, controlled, open-label, Phase 3, pragmatic, clinical and cost effectiveness trial with internal pilot. The target sample is 1956 critically ill adults. Participants will be equally allocated across four trial arms. All participants will receive usual airway clearance management. In three intervention groups, participants will receive either carbocisteine, hypertonic saline, or a combination of carbocisteine and hypertonic saline. In the fourth comparator group, participants will receive usual airway clearance management alone. The primary outcome is the duration of mechanical ventilation with secondary clinical, safety, and health resource utilisation outcomes. The trial will be reported in accordance with CONSORT guidelines. Ethical approval was granted by Leeds East (Yorkshire & The Humber) Research Ethics Committee (reference 21/YH/0234) on 28
^th^ October 2021. All participants will provide written, informed consent via either Personal or Professional Legal Representatives, and subsequently directly once capacity is regained.

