### Objectives

**
*Primary objective*
**

To conduct a large, UK, multi-centre, pragmatic, 2x2 factorial, randomised controlled trial to determine the clinical effectiveness (for duration of mechanical ventilation) of two mucoactives (carbocisteine or hypertonic saline), or a combination of both, when compared with usual airway clearance management. In keeping with the 2x2 factorial design, the main comparisons will be the use versus non-use of carbocisteine, and the use versus non-use of hypertonic saline.

**
*Secondary objectives*
**

When compared with usual airway clearance management, to:

1.   Determine the clinical effectiveness of carbocisteine or hypertonic saline, or a combination of both, on a range of secondary clinical and safety outcomes.

2.   Estimate, in an integrated economic evaluation, the cost-effectiveness of these mucoactives.

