### Statistical methods

The primary analysis will be conducted on outcome data from all randomised patients according to the group to which they were allocated (i.e. intention-to-treat), regardless of the subsequent treatment they received. Trial results will be reported in accordance with Consolidated Standards of Reporting Trials guidance (CONSORT)
^
37
^. It is possible that some participants may not receive the full treatment dose, therefore a secondary per protocol analysis will be undertaken on the population who receive the complete treatment dose. Baseline characteristics, follow-up measurements and safety data, will be described using suitable measures of central tendencies; means and medians with the associated standard deviations, 95% confidence intervals, and interquartile ranges for continuous data; and frequencies and proportions for categorical data (including binary data). 

Primary outcomes for the randomised groups will be compared using a Cox proportional hazards model including site and adjusting for age and illness severity (APACHE II). For this analysis, no interaction between interventions will be assumed. Comparison for other continuous outcomes will use analysis of covariance to adjust for baseline characteristics and covariates. Comparison for binary outcomes will use generalised linear models (GLMs) as appropriate to estimate risk ratio and risk differences. 95% CI and p-value will be presented alongside the estimates. Analyses will be two-sided and tested at an
*a priori* significance level of p=0.05. The factorial design permits separate testing of the effects of carbocisteine and hypertonic saline on outcomes. Although there is no biologic rationale for, or expectation that, either mucoactive will have an effect on death, a sensitivity analysis for competing risk of death will be included. Sensitivity analyses will also be included to investigate the impact of any potential interaction between the interventions on the primary analysis, to investigate the impact of contamination between the interventions, and to investigate the impact of compliance on the primary analysis. 

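### The sample size text gives the combination group a 6-day median, which contradicts the no-interaction assumption on which the 90% power depends

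*Protocol article*

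**What the plan says.** All references are to the Protocol article.

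- **Planning medians (Sample size).** "The sample size has been calculated using a median duration of mechanical ventilation of 7 days", with a minimal important difference of one day, "resulting in a median duration of 6 days in the three intervention groups".
- **Which groups these are (Abstract, Methods; repeated under Interventions).** In the three intervention groups, "participants will receive either carbocisteine, hypertonic saline, or a combination of carbocisteine and hypertonic saline". The combination is therefore one of the groups given a 6-day median.
- **Effect size and test (Sample size).** The effect is the ratio of the two medians: the "1 day reduction treatment effect result in a hazard ratio of 0.86". The calculation uses a log-rank test with 90% power and alpha 0.05. The resulting number is 1856 patients (464 per group), raised to 1956 (489 per group) for 5% loss to follow-up.
- **Interaction (Sample size; also Rationale for the intervention).** There is "no clinical or biological rationale for, or expectation of, any interaction between the two mucoactives", and the number was not inflated for one.
- **Main comparisons (Objectives).** "the main comparisons will be the use versus non-use of carbocisteine, and the use versus non-use of hypertonic saline".
- **Primary model (Statistical methods).** A Cox model; "For this analysis, no interaction between interventions will be assumed".

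**The concern.** In a 2x2 factorial trial analysed at the margins, each agent is tested by comparing the half of the patients who receive it with the half who do not. Half of the non-users of one agent receive the other agent. A hazard ratio of 0.86 between the two halves needs the agent to have its full effect both when given alone and when added to the other agent. That is what no interaction means, and it makes the combination better than either agent alone.

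The printed scenario says otherwise. If both agents together give 6 days and either alone also gives 6 days, the second agent adds nothing to the first. That is a complete sub-additive interaction, which the next paragraph of the same section says is not expected.

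The stated 90% power is therefore attached to a set of medians that does not deliver it. Anyone using the section to judge what the trial can detect is given a power figure for a different scenario. This includes the interim analysis, which is meant to check the sample size assumptions.

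**Working it through.** **Inputs.** From Sample size: medians of 7 and 6 days, hazard ratio 0.86 (6/7 = 0.857), 90% power, alpha 0.05, 1856 before and 1956 after loss. From Statistical methods: two-sided tests. From the sequence generation text: 1:1:1:1 allocation, so each margin is 928 v 928. From Outcomes: follow-up to 60 days. Assumptions made here: exponential times and every patient counted as an event. With exponential times and medians of 6 to 7 days, more than 99.7% of patients would have the event by day 60.

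**Step 1. Reproduce the plan's number.** Freedman's formula for 1:1 allocation:

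events = (1.960 + 1.282)² × [(1 + 0.86)/(1 − 0.86)]² = 10.507 × (1.86/0.14)² ≈ 1855

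Rounded up to a multiple of four this is 1856. Then 464/0.95 = 488.4, so 489 per group and 4 × 489 = 1956. Both figures reproduce. The 1856 is a two-group total, 928 v 928, with a hazard ratio of 0.86 across a whole margin. (Schoenfeld's formula gives 1848.)

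**Step 2. Combination median implied by no interaction.** With exponential times the median scales with the hazard ratio:

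- log-hazard scale: 7 × (6/7)² = 5.14 days (7 × 0.86² = 5.18 with the rounded ratio);
- additive in days: 7 − 1 − 1 = 5 days.

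Neither scale gives 6 days.

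**Step 3. Margin effect under the printed medians 7/6/6/6.** Take carbocisteine; hypertonic saline is symmetrical.

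| Hypertonic saline | Without carbocisteine | With carbocisteine | Log hazard ratio |
|---|---|---|---|
| No | 7 days | 6 days | ln(6/7) = −0.154 |
| Yes | 6 days | 6 days | 0 |

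The average is −0.077, so the margin hazard ratio is √(6/7) = 0.926.

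**Step 4. Power for each use-versus-non-use comparison.** Power = Φ(|ln HR| × √events / 2 − 1.96).

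- No interaction, 1856 events, HR 0.86: 0.1508 × 43.08 / 2 − 1.96 = 1.29, giving 90%. With HR 6/7: 91%.
- 7/6/6/6, 1856 events, HR √(6/7): 0.0771 × 43.08 / 2 − 1.96 = −0.30, giving 38%. With √0.86: 37%.
- 7/6/6/6, 1956 events: 40% with √(6/7), 38.5% with √0.86.

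**Step 5. Check by simulation** (exponential times, censoring at 60 days, 4000 runs).

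| Medians | Per group | Log-rank stratified by the other agent | Unstratified log-rank |
|---|---|---|---|
| 7/6/6/6 | 464 | 37% | 40% |
| 7/6/6/6 | 489 | 40% | 43% |
| 7/6/6/5.14 | 464 | 91% | 91% |

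**Step 6. Does another contrast make 90% true under 7/6/6/6?** One agent alone v usual care, 464 v 464, has 63-65% power. All three intervention groups pooled v usual care has about 80% at 1856 with HR 0.86. Neither reaches 90%, and neither is a main comparison under Objectives.

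**The case against.** The strongest reply is that the calculation is right and only a clause is loose. The number follows from a hazard ratio of 0.86 at each margin. The no-interaction premise is stated under Rationale for the intervention, Sample size and Statistical methods. The 6-day clause could be meant as the smallest effect of a treatment worth detecting against 7 days, not as a forecast for each of the four groups. Most of this stands: 1856 and 1956 are correct for the design, and 37-40% applies only if the printed medians are taken literally. It does not remove the fault, because the clause names all three intervention groups, and the combination is one of them.

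A reader might infer three stronger things that the document does not support:

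- **That the trial has only about 38% power, or too few patients.** Under the stated no-interaction premise it has 90-91%. The wrong element is the combination median, not the sample size.
- **That low power for one agent v usual care, or for the interaction, is a further error.** The plan claims no power for either. It says openly that it did not inflate for interaction, and it plans a sensitivity analysis for one. Lower power within single groups is inherent in a factorial trial analysed at its margins.
- **That a null main effect would be misread as ineffectiveness.** No such rule is given for the factorial comparisons. How main effects are read beside an interaction estimate is properly left to the SAP, which is not shown.

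**Conclusion.** The point holds as an internal inconsistency. The printed planning scenario of 7/6/6/6 cannot be reconciled with the no-interaction assumption on either the hazard or the day scale. Without interaction the combination median would be about 5.1 days (5 if effects add in days). The 90% belongs to that scenario. Under the printed medians the margin hazard ratio is about 0.93 and power is about 37-40% by formula across 1856 to 1956 events; simulation gives 37-43%.

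The contradiction itself needs no distributional assumption beyond one-day effects that either multiply on the hazard scale or add in days. The 5.1 days and the power figures assume exponential times and nearly complete events by day 60. The consequence is a misdescribed planning scenario and a power figure attached to the wrong medians.

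**What to change.** In Sample size, replace the clause on the 6-day median with text such as:

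> a median of 6 days with each agent alone and about 5.1 days with both, assuming no interaction on the log-hazard scale (HR 0.86 per agent); 90% power applies to each use-versus-non-use comparison, 928 v 928. If the combination median is only 6 days, power for these comparisons falls to about 37-40%.

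Keep 0.86 in the wording, because that rounded value is what yields 1856. The unrounded 6/7 needs only about 1776 events by the same formula and would introduce a new mismatch.

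The sample size, the test, the main comparisons and the primary model do not change, and no extra patients are needed. With 1820 of 1956 enrolled at the date given under Trial status, this matters for the record and for readers of the results. The cost is one rewritten sentence and a less favourable power figure stated openly for the sub-additive scenario.
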